## Abstract

**Background:**

Fatigue is a common problem that significantly affects intensive care unit (ICU) survivors’ physical, psychological, and social functioning. ICU survivors often experience a loss of self-worth and identity, struggle to return to their normal roles, and face ongoing challenges with cognitive and emotional recovery. Despite its profound impact, there are limited rehabilitation interventions targeting this population. This research aims to evaluate the acceptability of implementing the Fatigue After CriTical illness (FACT) self-management intervention into usual care for patients experiencing fatigue after critical illness and the feasibility of the intervention for a future clinical trial.

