## Aims and objectives

This study aims to determine the feasibility and acceptability of conducting a randomised controlled trial (RCT) of the FACT intervention. The objectives are:Primary objective: To assess the willingness of people affected by fatigue after critical illness to participate in an RCT evaluating an HCP-supported self-management intervention for fatigue after critical illness.Secondary objectives:To estimate recruitment, retention, and the variability of outcome measures to inform sample size calculations and choice of outcome measures for a future effectiveness trial.To evaluate the acceptability and fidelity of the intervention by assessing adherence, estimated frequency of visiting the website, and patterns of use.To evaluate HCPs’ perceptions and experiences of delivering support for this intervention.

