#### Primary outcome measures

The primary outcome focuses on the willingness of people affected by fatigue after critical illness to participate in an RCT evaluating an HCP-supported, self-management intervention. Recruitment and retention rates are critical indicators.

Recruitment rate is defined as the number of participants recruited or randomised as a proportion of those eligible and approached. This rate will be assessed at baseline and calculated both overall and by the research site.

Retention rate is defined as the proportion of participants who complete all the required questionnaires and semi-structured interviews. This outcome is essential to evaluate participant engagement and the feasibility of collecting follow-up data.

Assessments will be completed via phone or video call at baseline, three months, and six months post-randomisation. During the baseline data collection phase, additional demographic information (including age, sex, ethnicity, employment status, and marital status) and medical history (including comorbidities, primary diagnosis on ICU admission, ICU length of stay, hospital length of stay, days of mechanical ventilation, and severity of illness assessed by the APACHE III [22] will also be collected.

The progression criteria for full trial are summarised in Table 1.

**Table 1 Tab1:** Progression criteria

Category	Recruitment	Retention and follow-up completion	Remedial action
Green (Go)	> 85% anticipated (> 60 participants)	At least 80% of survivors will provide complete follow-up data	Continue—no action needed. Apply for further funding
Amber (Amend)	50–85% anticipated (36–75 participants)	60–80% of survivors will provide complete follow-up data	Continue—action needed. Explore ways to improve recruitment/retention
Red (Stop)	< 50% anticipated (< 35 participants)	< 60% of survivors will complete follow-up data	Stop. Explore reasons for poor recruitment/retention

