
Additionally, to evaluate the acceptability and fidelity of the intervention will be evaluated using a combination of quantitative and qualitative methods six months after randomisation. Participants will complete the Theoretical Framework for Acceptability Questionnaire (TFAQ) [32] and the System Usability Scale (SUS) [5] to assess their perceptions of the intervention and the usability of the digital platform.

Theoretical Framework for Acceptability Questionnaire (TFAQ) [32]TFAQ Comprises: Section 1 (All participants) including 6 items covering affective attitude, burden, ethicality, self-efficacy, opportunity costs, and general acceptability and Section 2 (Intervention group only) including 8 items covering the same plus perceived effectiveness and intervention coherence Responses are on a 5-point Likert scale from 1 to 5.System Usability Scale (SUS) [5]The SUS contains 10 items measuring system usability. Responses range from 1 (“strongly disagree”) to 5 (“strongly agree”). Items alternate between positively and negatively worded statements. Question 2, 4, 6, 8, and 10 are reverse scoring.Digital analytics, including the completion of sections from the intervention website will be used to measure patterns of engagement with the intervention components. These data will be collected at the 6-month follow-up and will be included in the evaluation of compliance level.

To be more specific, participants in the intervention group will be evaluated for compliance based on four categories: high compliance, moderate compliance, limited compliance and non-compliance, as summarised in Table 2. Highly compliant participants are those who complete at least 10 sections (66.66% or more) of the intervention, receive the supportive phone call, and set a personal goal with an action plan. Moderately compliant participants complete between 6 and 9 sections of the intervention and fulfil at least one secondary requirement, such as receiving the supportive phone call or setting a personal goal with or without an action plan. Limited compliant participants complete fewer than 5 sections (33.33% or less) but meet at least one secondary requirement. Participants who do not satisfy the criteria for a given category will be classified in the next lower level of compliance, with non-compliant participants being those who fail to meet the criteria for limited compliance.

**Table 2 Tab2:** Details for compliance levels

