### Data analysis

#### Quantitative

Assessments will be performed at baseline, three months, and six months post-randomisation to evaluate feasibility and acceptability. Descriptive statistics will be employed to summarise the baseline demographic and clinical characteristics of both groups. Categorical variables will be reported as frequencies, percentages, and 95% confidence intervals (CI). Continuous variables that are approximately normally distributed will be summarised as means with standard deviations (SD) and 95% CIs. Continuous variables that are non-normally distributed will be summarised using medians with interquartile ranges (IQR).

Feasibility outcomes (including recruitment and retention) will be analysed using descriptive statistics only, consistent with feasibility study methodology. These outcomes will be compared against the pre-specified progression criteria to determine whether they are practical and appropriate to proceed to a definitive RCT.

An analysis of data in the questionnaires will explore potential differences between the groups and whether there is a difference in the change between the groups before and after the intervention to assess the effectiveness of the intervention in reducing fatigue and improving overall quality of life.^1^ Analyses will be conducted based on intention-to-treat (ITT). As this is a small study, treatment effects are likely to have wide CIs and consequently inferences will be tentative and reported as such. Results will be reported in accordance with CONSORT extension to randomised pilot and feasibility trials [16]. A summary of outcome measures, data types, and analysis is listed in Table 3.

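### The progression rule in Table 1 has no criterion for uptake or delivery of FACT, so low uptake or undelivered calls cannot alter the formal decision

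*Protocol article*

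**What the plan says.** Under Aims and objectives the protocol article states: "This study aims to determine the feasibility and acceptability of conducting a randomised controlled trial (RCT) of the FACT intervention". The primary objective is willingness to take part in such a trial. A secondary objective reads: "To evaluate the acceptability and fidelity of the intervention by assessing adherence, estimated frequency of visiting the website, and patterns of use". The abstract's Background also names the intervention itself: "This research aims to evaluate the acceptability of implementing the Fatigue After CriTical illness (FACT) self-management intervention into usual care".

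The section on secondary outcome measures provides the tool for that objective: "participants in the intervention group will be evaluated for compliance based on four categories". Table 2 builds the categories from website sections completed, receipt of the supportive call, and goal setting with or without an action plan. An acceptability questionnaire (TFAQ), a usability scale (SUS) and interviews sit alongside.

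The progression criteria are in Table 1, under primary outcome measures. Its columns are "Category Recruitment Retention and follow-up completion Remedial action". Green for recruitment is "> 85% anticipated (> 60 participants", and Green for follow-up is complete data from at least 80% of survivors. The Green action is "Continue—no action needed. Apply for further funding". The Amber and Red actions mention only recruitment and retention. The quantitative analysis section then says of the feasibility outcomes: "These outcomes will be compared against the pre-specified progression criteria to determine whether they are practical and appropriate to proceed to a definitive RCT".

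**The concern.** A feasibility trial of a self-managed intervention has to settle two things before a definitive trial: whether people will enter and stay, and whether those offered the intervention use it and receive the planned support. The article plans to measure both but lets only the first count in the decision. No threshold is given for compliance, call delivery, TFAQ or SUS, and no text says how the Table 2 distribution would affect the decision.

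At stake is the recommendation, not the data. A definitive trial could be recommended with an unqualified Go after poor uptake or poor delivery, and it would then compare usual care with an intervention that many participants barely received. Even an Amber result points only to recruitment and retention remedies, so the formal rule never directs attention to the intervention.

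**Working it through.** **Inputs.** Target 70, allocated 1:1, so 70/2 = 35 in the intervention arm (Sample size). Green needs more than 85% of anticipated recruitment (more than 60 participants) and at least 80% of survivors with complete follow-up (Table 1). Retention means completing all required questionnaires and interviews (Primary outcome measures).

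**1. Reproduce the plan's own counts.** 0.85 × 70 = 59.5, against the stated 60. 0.50 × 70 = 35, against the stated 35. Table 1's recruitment percentages therefore refer to the target of 70.

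**2. Apply the rule.** Assume all 70 are recruited and all survive.
- Recruitment: 70/70 = 100%, above 85%, so Green. The printed Amber count band runs from 36 to 75 and overlaps Green. That is a separate slip; by percentage the reading is clear.
- Follow-up: 56/70 = 80%, which meets the Green wording. The Amber band also ends at 80%, so to move off the shared boundary take 57/70 = 81.4%. The result is the same.

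**3. Vary uptake with everything else fixed.**

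| Intervention participants at Moderate or High compliance | Recruitment | Follow-up | Table 1 result |
|---|---|---|---|
| 0/35 (0%) | Green | Green | Green |
| 14/35 (40%) | Green | Green | Green |
| 28/35 (80%) | Green | Green | Green |
| 35/35 (100%) | Green | Green | Green |

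Uptake is not an argument of the rule, so no value changes the outcome. The same holds for the number of supportive calls delivered.

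**4. Check for an indirect route.** Low use could reduce completion of the SUS or of the intervention-only part of the TFAQ, and so lower retention. But nothing makes completion conditional on having used FACT, so a low user who answers every questionnaire counts as retained.

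**5. What could 35 participants say about uptake?** Exact (Clopper-Pearson) 95% limits: lower = Beta quantile(0.025; x, n − x + 1), upper = Beta quantile(0.975; x + 1, n − x). For x = 0 the lower limit is 0 and the upper is 1 − 0.025^(1/35) = 0.100.

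| x/35 | Estimate | Exact 95% CI |
|---|---|---|
| 0 | 0% | 0 to 10.0% |
| 14 | 40% | 23.9 to 57.9% |
| 21 | 60% | 42.1 to 76.1% |
| 28 | 80% | 63.1 to 91.6% |

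This separates poor from good uptake but cannot place a cut-point finely.

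**6. Is Table 2 ready to carry a decision?** Not yet.
- Moderate needs more than 5 sections and Limited fewer than 5, so exactly 5 fits neither count band.
- The Intervention section gives 16 sections: 10/16 = 62.5% and 5/16 = 31.25%. The stated 66.66% and 33.33% correspond to 10/15 and 5/15.
- Section completion comes from website analytics, yet a printed booklet is offered. Booklet users may be counted as not completing sections, and of the three problems this could distort a Moderate-or-High proportion most directly.

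**The case against.** The strongest reply is that Table 1 does what its section promises. The primary objective and outcome are willingness to take part, with recruitment and retention as the indicators, and adherence, acceptability and fidelity are secondary. The action column is about recruitment and retention, so the Green entry may mean only that no remedy is needed on those two. The Outcome measures section says primary and secondary outcomes inform the later trial, and the Discussion says the findings will help support adherence and delivery. The management group meets every four weeks and would probably notice that calls were not being made. The article also condenses a fuller protocol.

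Much of this stands. This is an omission from a decision rule, not a contradiction, and uptake will be measured and reported. But statements that findings will inform a later trial do not bind the rule, and the quantitative analysis section makes comparison with the stated criteria the basis for proceeding. Table 3 is not shown, but it is captioned as a summary of the analysis plan, and the article points to Table 1 for progression.

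A reader might infer three stronger things that the documents do not support:
- **That the rule ignores half of the trial's aim.** The aim sentence concerns the feasibility and acceptability of conducting an RCT, and acceptability of the intervention is a secondary objective.
- **That the criteria are diluted because half of the participants are controls.** Willingness to be randomised and retention have to be assessed in both arms.
- **That an unused intervention would go forward unchanged.** Complete non-use alongside 80% follow-up is unlikely, and the article says it will use its findings in designing the later trial.

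**Conclusion.** The point holds as a gap in the decision rule. Once both Table 1 columns are Green, the formal result is the same for any uptake from 0/35 to 35/35 and for any number of calls delivered, although the article names acceptability and fidelity as an objective and already plans a measure of compliance. The zero-use row only illustrates the limit; the practical risk is middling uptake, such as 40%, passing without comment from the rule.

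This should be changed, but it does not threaten the validity of the data or the primary objective. The conclusion assumes that Table 1 is the whole progression rule, as the article presents it, and that the Green action is applied as printed. If the full protocol holds a further criterion, the article should show it.

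**What to change.** Reconcile Table 2 first: assign exactly 5 sections to a category, correct the percentages against 16 sections, and state how section completion is counted for booklet users.

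Then add an intervention-arm criterion to Table 1: the proportion at Moderate or High compliance, with supportive-call delivery reported beside it. The team should justify its own cut-points. The 80% and 60% bands for follow-up were set for questionnaire completion and have no stated rationale for uptake. The cut-points should be dated before the 6-month compliance data are examined, or else labelled post hoc; final assessments and analysis are due by May 2026, so this matters now. State that a below-Green result caps the overall decision at Amber, with an action directed at the intervention or its delivery.

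The cost is one added criterion and the Table 2 repair. For website users the data are already planned; booklet users may need a simple way of recording completion. Green becomes harder to reach. With 35 participants the estimate is imprecise, which is why the criterion should guide amendment and should not stop the programme alone.

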### Study design

The study is a multicentre, open-label, feasibility RCT, with a qualitative evaluation of acceptability, conducted across ICUs at three UK NHS Trusts. A total of 70 participants will be randomised in a 1:1 ratio by sealed envelopes to receive the FACT intervention in addition to usual care or usual care alone. The intervention will be made available to the patients on hospital discharge and be accessible for 6 months. Participants will have a 30-min supportive phone/video call with an HCP from the ICU follow-up team at each site for three months. HCPs will attend an online training event and follow a defined protocol to facilitate goal-setting and personal action-planning. This study is an open-label trial; therefore, there will be no blinding to the participants or the trial management team.

All participating research sites offer inpatient ICU follow-up services. Patients who were in the ICU for more than 72 h are offered outpatient services at three months after hospital discharge, where physical and psychological health outcomes are evaluated. Where necessary, appropriate referrals and treatment plans are made. In the control group, patients (*n* = 35) will receive standard care, which includes routine follow-up services at their respective sites. Standard care typically involves a review of the patient’s recovery status without any additional interventions provided by the study. Additionally, patients may access generic information about recovery after critical illness, which is available on a variety of websites, including resources addressing fatigue. A flow chart of the study is presented in Fig. 1.

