### Sample size

Based on our case-mix data, we have a target sample of 70 participants with 1:1 randomised to the intervention and control arms. As this is a feasibility trial, a power calculation has not been conducted. Seventy participants would provide adequate feasibility data [35] and allow timely completion of the study. Anticipating a participant retention rate of 80%, we estimated that a target sample of 70 would allow us to calculate retention with a margin of error of approximately 18% with a 95% confidence level. This sample size was deemed sufficient to inform the future RCT and to provide adequate analysis of the study’s progression criteria.

HCPs involved in the delivery of the intervention at each site will be purposely sampled from each site. It is anticipated that 2–5 HCPs from each site will be involved in the intervention delivery. Eligible HCPs will include those registered with a professional body (Nursing and Midwifery Council, General Medical Council, Health, and Care Professionals Council) and who are directly involved in the delivery of the intervention for this study.

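### Table 1's Amber recruitment counts (36–75) do not match 50–85% of the target of 70, so totals of 61–70 are both Green and Amber, 60 depends on the reading, and 35 has no count band

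*Protocol article*

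**What the plan says.** The Sample size section sets the recruitment goal: "we have a target sample of 70 participants with 1:1 randomised to the intervention and control arms". The Study design section repeats it: "A total of 70 participants will be randomised in a 1:1 ratio by sealed envelopes".

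Table 1, under Primary outcome measures, gives three recruitment bands, each as a percentage with a count in parentheses:

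- Green: "> 85% anticipated (> 60 participants"
- Amber: "50–85% anticipated (36–75 participants"
- Red: "< 50% anticipated (< 35 participants"

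The remedial-action column attaches a different instruction to each. Green means carry on with nothing to change and seek funding. Amber means carry on but look for ways to improve. Red means stop. For retention, Green starts at 80% of survivors inclusive, Amber runs from 60% to 80%, and Red is below 60%.

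The Quantitative part of Data analysis makes this table the yardstick: "These outcomes will be compared against the pre-specified progression criteria to determine whether they are practical and appropriate to proceed to a definitive RCT". The article does not say whether the percentage or the count governs, or which band applies when a result fits two.

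**The concern.** In a feasibility trial the progression criteria are the main decision rule, and their value lies in being fixed before the totals are known. For that, each possible result has to fall in exactly one band. The Amber count range runs past the recruitment target and over the whole part of the Green range that the trial can reach within that target. The results the trial hopes for, including full recruitment, therefore carry two different instructions if the counts are used. Whoever applies the table would have to decide which reading to follow, possibly with the total already in hand.

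**Working it through.** **Inputs.** Target N = 70 (Sample size; Study design). Percentage limits 50% and 85%, and count limits 35, 36, 60 and 75 (Table 1). I take the percentages in Table 1 to be percentages of the 70, since the counts beside them are participants recruited. No power calculation is involved ("As this is a feasibility trial, a power calculation has not been conducted"), and none is needed for this check.

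**Step 1: try to reproduce the count limits as percentage × 70.**

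- 0.50 × 70 = 35. The Red limit of 35 is reproduced exactly. The Amber lower limit of 36 is one participant away (36/70 = 51.4%).
- 0.85 × 70 = 59.5. The Green limit of 60 is within one participant (60/70 = 85.7%).
- The Amber upper limit of 75 is not reproduced: 75/70 = 107.1%.

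**Step 2: see whether another target explains the limits.** Implied target = count limit ÷ percentage.

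- 35/0.50 = 70
- 36/0.50 = 72
- 60/0.85 = 70.6
- 75/0.85 = 88.2

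Three of the four lie at or near 70. No single target yields all four, and 75 is the one far out.

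**Step 3: classify every total from 0 to 70 both ways.**

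| Total recruited | By printed count | By percentage of 70 |
|---|---|---|
| 0–34 | Red | Red |
| 35 | no band | Amber (exactly 50%) |
| 36–59 | Amber | Amber (51.4% to 84.3%) |
| 60 | Amber | Green (85.7%) |
| 61–70 | Green and Amber | Green (87.1% to 100%) |

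The readings differ at 35, at 60 and at the ten totals 61–70: 1 + 1 + 10 = 12 of 71 possible totals. They agree at the other 59 (35 totals in 0–34 and 24 in 36–59).

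**Step 4: does correcting 75 alone suffice?** No. With an Amber upper limit of 60, a total of 60 is still Amber by count and Green by percentage. With an upper limit of 59, a total of 60 has no count band, because Green starts above 60. In either case 35 remains unassigned by count.

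**Step 5: retention.** Exactly 80% satisfies both the Green and the Amber condition. With S survivors, 0.80 × S is a whole number only when S is a multiple of 5, so the shared edge is one result for some values of S and cannot occur for the others.

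**The case against.** The strongest reply is that 75 is a slip in a parenthesis and the scheme itself is sound. The percentages come first in each cell, and with 70 as the base they divide the recruitment scale with no overlap and no gap. Three of the four count limits agree with 70 exactly or to within one participant. Full recruitment is 100% of target, so it can be called Amber only by ignoring the percentage in the same cell. Green and Amber also both allow the work to continue. Recruitment and retention are summarised descriptively, so no estimate or test is affected.

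Most of this is fair, and it limits the point. It does not remove it, because the article never says that the percentages override the counts, and Step 4 shows that correcting 75 alone leaves 35 and 60 unsettled. The discrepancy at 60 is only rounding, but a threshold has to fall on one side or the other.

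A reader might infer more than the documents support:

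- *That the Go/Amend/Stop decision cannot be read at all.* It can for 0–34 and 36–59, where the two readings agree.
- *That every Green count is also Amber.* This is true only up to the target. Green has no printed upper limit, so 76 or more would be Green alone.
- *That a Stop could become a Go.* No total is both Red and Green under either reading.
- *That the verdict will be picked after the data are seen.* This is a risk. The article does commit to comparison with criteria fixed in advance.
- *That 56 of 70 retained would fall in two bands.* Retention in Table 1 is a share of survivors, so this needs full recruitment and no deaths. The double assignment holds at exactly 80% of whatever number survive.

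**Conclusion.** The Amber count range is wrong as printed: its upper limit is 107% of the target, where its own percentage gives 59.5. By the counts, all ten Green totals reachable within the target are also Amber, 35 belongs to no band, and 60 changes band with the reading. The practical effect is uncertainty between Go and Amend at 60–70, and one unassigned total at the lower edge of Amber.

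This rests on the percentages being taken of 70, which the target and three of the four count limits support. The three recruitment cells read coherently in the text available, so damage in extraction is unlikely. The shared 80% retention edge is a minor wording matter. The correction still matters, because this table is the stated basis for deciding on a definitive trial and the affected totals include full recruitment.

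**What to change.** Before the criteria are applied, state in Table 1 that the percentages of the target of 70 govern, and restate the counts from them:

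- Recruitment: Green ≥60 (>85%), Amber 35–59 (50–85%), Red ≤34 (<50%).
- Retention among survivors: Green ≥80%, Amber ≥60% to <80%, Red <60%.

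These bands neither overlap nor leave a gap, and no limit exceeds the target. Compared with the printed counts, they put 35 in Amber and 60 in Green and remove Amber from 61–70. Because the article does not say which figure was meant to govern, the sponsor should confirm that the percentages are the intended limits. The cost is a correction to one table, with no change to recruitment, follow-up or data collection.
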